**Randomization**

Since the diversity of the patients included in the study, after signing the informed consent is expected to be high, no stratifies criteria will be used. Patients will be randomized in 1:1 fashion to either treatment or controlled-cross group.

There will be no placebo in the cross group during the control period. The only way to give “placebo” of HBOT, is to bring the patients to the hyperbaric chamber and to increase the environmental pressure in a way the patients will “feel the hyperbaric pressure” in their ears. However, Henry’s law states: “the amount of a given gas dissolved in a given type and volume of liquid is directly proportional to the pressure of that gas in equilibrium with that liquid”. Thus, hyperbaric environment significantly increases the dissolved oxygen pressure even if a person holding his breath [[29](#_ENREF_29)]. Moreover, the alternative of hosting the patients in the hyperbaric chamber without any pressure increase cannot serve as a real placebo since the patients will not feel the pressure. Accordingly, the only real “placebo” could be achieved by increasing the pressure and reducing the percentages of the oxygen but that holds significant safety consideration.

From the ethical point of view, it is deemed unethical to “treat” the patients (40 sessions in the hyperbaric chamber) while they actually know that it is a placebo. In order to somewhat compensate for this limitation, the control will be a cross group and after the 2^nd^ evaluation at the end of a control period they will be crossed to HBOT. The cross for treatment enables intra-group efficacy evaluation in both treatment and control group.

Since the patients will know they are not receiving HBOT during the control period they will not be blinded with regard to the treatment arm. Accordingly, the quality of life evaluations will not be blinded. However, the complete blindness evaluation can be assured in both of the primary end points of this study, The Mindstreams computerized evaluation and the brain SPECT evaluation done by the radiologist.

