Hyperbaric Oxygen Therapy (HBOT) has been in use since the 1930's when it was initially used for decompression sickness. Shortly thereafter physicians started using HBOT for a variety of other conditions. The use of HBOT for neurological indications started in the early 1960's with the work by Smith et al showing its protective effect in cerebral ischemia and that of Saltzman showing effectiveness in stroke patients [[8](#_ENREF_8)]. HBOT is the inhalation of 100% oxygen at pressures exceeding 1 atmosphere absolute (ATA) in order to enhance the amount of oxygen dissolved in the blood and body fluids, thereby allowing for increased oxygen delivery to the tissues. Under normobaric conditions, the amount of oxygen dissolved in the blood is only 0.3 ml/dl. At 1.5 ATA this amount increases 10 fold to 3.2 ml/dl. Using an animal model of brain injured mice Daugherty et al. [[9](#_ENREF_9)] found a 250% increase in the local brain tissue oxygen levels between 100% oxygen administered at 1 ATA (103 mmHg) as opposed to that given at 1.5 ATA (247 mmHg). This seems to suggest that dissolved O2 is more readily available to the brain tissue than hemoglobin bound oxygen [[10](#_ENREF_10)]. Additionally, work by several investigators seems to indicate that HBOT allows for more efficient use of baseline oxygen levels by injured brain tissue following treatments, which in turn leads to a positive persistent affect on this tissue [[10](#_ENREF_10)].

The mechanism by which HBOT is thought to improve the outcome of brain injury is multifaceted, The Neubauer and Walker theory postulates that HBOT improves cerebral metabolism by improving functioning of the dormant neurons and stimulating axonal growth [[11](#_ENREF_11)]. Zhang et al suggest that potential targets of oxygen therapy include prevention of apoptosis, inhibition of neuroinflammation and BBB damage [[12](#_ENREF_12)] . There is stimulation of angiogenesis and neovascularization, as well as direct effects on blood vessels in the brain, and maintenance of BBB integrity [[10](#_ENREF_10),[13](#_ENREF_13)]. Similarly, SPECT scans have demonstrated a positive effect on the cerebral blood flow (CBF) in the damaged brain following HBOT [[10](#_ENREF_10),[11](#_ENREF_11),[14](#_ENREF_14),[15](#_ENREF_15),[16](#_ENREF_16" \o "Neubauer, 1990 #402)].

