**Objectives**

The aim of the current study is to evaluate, for the first time in a prospective cross-over, randomized study, the effect of hyperbaric oxygen therapy (HBOT) on patients with chronic neurocognitive deficiency due to mild TBI.

- The primary endpoints of the study are to evaluate the effects of the HBOT on:
- Neurocognitive function (using Mindstreams neurocognitive battery)
- Brain metabolism (as visualized by SPECT)
- The secondary endpoints included quality of life evaluation.

The safety of the HBOT in this post TBI population will also be evaluated and any adverse event will be recorded.

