***Study protocol***

After signing the informed consent, patients will be randomized in 1:1 manner into the treated or the control-cross group. After the randomization, patients will be invited for baseline evaluation that will include full review of their medical status and complete physical examination. All patients will present baseline anatomical scan (CT/MRI). After their inclusion, patients will be randomized to two groups: a treated group and a cross group. All patients will go through evaluation of their neurocognitive function using neurocognitive testing battery, quality of life using EQ-5D questionnaire and brain functional imaging (rCBF-SPECT scan). The patients in the treated group will be evaluated twice – at baseline and after 2 months of HBOT treatment. The patients of the cross group will be evaluated three times – at baseline, after a 2 month control period of no treatment and after a consequent 2 month period of HBOT treatment. We emphasize that the study will be a cross-over trial and patients in the cross group will receive HBOT treatment after their second evaluation and will go through a third neurological evaluation after the cross, when they will complete their HBOT.

The following HBOT treatment protocol will be practiced: The patients will go through 40 HBO treatments (each treatment session will be given on a separate day), distributed over two months (five days a week). Each session will be for 60 minutes in 100% oxygen atmosphere and at pressure of 1.5 ATA.

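### An open no-treatment comparator, with efficacy also judged within groups, cannot support an oxygen-specific conclusion; the claim should rest on the randomised month-2 comparison and be limited to the HBOT course

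*Protocol*

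**What the plan says.** **Aim.** The Objectives section sets out to evaluate "the effect of hyperbaric oxygen therapy (HBOT) on patients with chronic neurocognitive deficiency due to mild TBI". The Background defines HBOT as breathing pure oxygen above 1 ATA.

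**Arms.** Under Study protocol, the treated group has 40 sessions on separate days over two months, each 60 minutes of 100% oxygen at 1.5 ATA. The cross group has two months without treatment, then the same course. The cross group is evaluated three times, the treated group twice.

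**No placebo.** The Randomization section gives four reasons:
- Pressure by itself raises dissolved oxygen, by Henry's law: "Thus, hyperbaric environment significantly increases the dissolved oxygen pressure even if a person holding his breath".
- A chamber stay without pressure would not be felt.
- Raised pressure with a reduced oxygen percentage would be a real placebo but raises safety issues.
- It is unethical to give 40 sessions to patients who know that they are on placebo.

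The section calls the missing placebo a limitation and says that the cross compensates for it in part: "The cross for treatment enables intra-group efficacy evaluation in both treatment and control group". It accepts that patients know their arm and that quality of life is therefore unblinded, but holds that blind evaluation is assured for both primary endpoints.

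**Oxygen figures.** The Background states "Under normobaric conditions, the amount of oxygen dissolved in the blood is only 0.3 ml/dl", and then "At 1.5 ATA this amount increases 10 fold to 3.2 ml/dl".

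**Test.** The Primary Efficacy Analysis section sets p1, improvement attributed to the HBOT training (0.12), against p2, improvement from retesting (0.02). Success is declared when the lower confidence limit for HBOT success is at or above 0.12.

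**The concern.** The two arms differ in several things at once during the randomised period: oxygen, pressure, 40 supervised attendances, and knowledge of being treated. Oxygen under pressure is the only one of these named in the definition of HBOT. The aim is worded without qualification, and the hypotheses allow for one non-treatment effect only, retesting. Attention and expectation get no allowance, although the first primary endpoint is a test that the patient performs knowing the arm. Scoring by computer masks the assessor, not the patient's effort.

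The section offers the cross as the partial remedy. If the intra-group changes are read as efficacy evidence, an open before-after change could be reported as an effect of hyperbaric oxygen. The stated success rule points the same way, because it is met or missed on HBOT data alone.

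**Working it through.** **1. What each contrast can remove**

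| Contrast | Retest and natural course | Attendance, attention, expectation |
|---|---|---|
| Treated group, before to after HBOT | not removed | not removed |
| Cross group, before to after HBOT | not removed | not removed |
| Cross group, HBOT-period change against its own no-treatment change | partly (HBOT always comes second) | not removed |
| Randomised arms at month 2 | removed | not removed |
| Success rule (lower limit of HBOT success against 0.12) | only through the assumed 0.02 | not removed |

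No row isolates oxygen. Only the randomised month-2 row supports a causal statement, and that statement concerns the whole course: 40 × 60 min = 40 hours of chamber time in the treated arm against no chamber sessions in the control arm.

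**2. The Background's oxygen figures**

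Reproducing the stated rise: 3.2 / 0.3 = 10.7, consistent with 10-fold. Active rise: 3.2 − 0.3 = 2.9 ml/dl.

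Pressurised air at 1.5 ATA, computed in two ways:
- *Strict proportionality, as the protocol cites Henry's law:* 0.3 × 1.5 = 0.45 ml/dl. The rise is 0.15, which is 50% over baseline and 0.15 / 2.9 = 5% of the active rise.
- *Straight line through the two Background values, taking air as 21% oxygen (assumption):* slope 2.9 / (1.5 − 0.21) = 2.25 ml/dl per ATA of inspired oxygen. Air at 1.5 ATA has 0.315 ATA. The rise is 0.105 × 2.25 = 0.24 ml/dl, to 0.54, which is about 80% over baseline and 0.24 / 2.9 = 8% of the active rise.

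Pressure without added oxygen therefore does raise dissolved oxygen, but more than 90% of the active rise comes from the 100% oxygen.

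**3. What an unallowed-for non-specific effect could do (illustration)**

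Read 0.02 and 0.12 as proportions of patients who improve, as the binomial sample size does, and take n = 31. An exact one-sided test of 0.02 at 0.05 rejects with 3 or more improvers: P(X ≥ 3 | 0.02) = 0.024, while P(X ≥ 2 | 0.02) = 0.127. If oxygen did nothing and non-specific effects alone gave the rates below (assumed values), P(X ≥ 3) would be:

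| Assumed rate | 4% | 6% | 8% | 10% | 12% |
|---|---|---|---|---|---|
| Chance of rejecting 0.02 | 13% | 28% | 46% | 61% | 74% |

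This concerns the stated hypothesis p1 > p2. The literal success rule is stricter (3/31 = 9.7% is already below 0.12), so these chances do not apply to it.

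**4. Power of the randomised comparison on the protocol's own rates**

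For 0.12 against 0.02, one-sided 0.05 and 80% power, n per arm = [1.645 √(2 × 0.07 × 0.93) + 0.842 √(0.12 × 0.88 + 0.02 × 0.98)]² / 0.10² = 79.4, so 80. With 31 per arm the power is 46%; with 15 per arm, 28%. The protocol does not say whether N = 31 is a total or a per-arm number.

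**The case against.** The best defence is that the protocol is open about this. It calls the missing placebo a limitation, says the cross compensates only in part, and admits that patients are not blinded. The word training in the definition of p1 fits a treatment course at least as well as an oxygen-specific effect. The cross group's three evaluations also do real work: a change under no treatment can be set beside a change under HBOT in the same patients, which speaks to retesting and natural course. All of this stands. It does not cover attention or expectation, and the admission about blinding stops at quality of life.

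A reader might infer that the Background figures contradict the Henry's law argument, so that the sentence should be deleted. They do not. A rise of 50 to 80% over baseline is a rise, and a pressurised-air control would not be oxygen-neutral. The Background also reports animal brain-tissue oxygen of 103 mmHg at 1 ATA and 247 mmHg at 1.5 ATA, a ratio of 2.4. Both values are on 100% oxygen, so they suggest that pressure matters but say nothing direct about pressurised air.

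A reader might also infer that the protocol has no valid reason for omitting a placebo. The safety reason is separate, and the oxygen figures do not touch it. The ethics sentence is the weak one: it assumes that patients know they receive placebo, which a masked control would avoid.

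Finally, a reader might infer that controls have no contact at all. The protocol says no treatment; it does not describe other contact during the control period.

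**Conclusion.** The point holds in a limited form. The design can support a conclusion about a 40-session HBOT course against no treatment, open label, and only through the randomised month-2 comparison. It cannot support an oxygen-specific conclusion, and the cross does not change that, because intra-group changes carry the same attendance and expectation effects. The success rule as written does not use the control arm, so it does not deliver even the course-level comparison.

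The Henry's law reason is weak in size (about 5% of the active rise by strict proportionality, about 8% by the straight line with air at 21% oxygen) but not refuted. How large any non-specific effect would be cannot be known from the protocol; the 13% to 74% range rests on assumed rates of 4% to 12%. An open control is not in itself an error here. What needs correcting is the unqualified aim and attribution, and the efficacy role given to intra-group results.

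**What to change.** - In Objectives, Primary Efficacy Analysis and Randomization, state that the efficacy conclusion rests on the randomised between-arm comparison at month 2. Limit it to a 40-session HBOT course versus no treatment, open label, with no oxygen-specific claim.
- Label the cross group's change after HBOT, and all other intra-group before-after results, as descriptive. Say that they may inform on retesting and natural course but do not compensate for the missing placebo.
- Restrict the blinding statement for the cognitive endpoint to its scoring, and note that patients know their arm when they take the test.
- Reconcile the placebo reasoning in Randomization with the Background figures: give the size of the pressure-only rise with its assumptions, keep the safety reason distinct, and correct the ethics sentence. No sham procedure is proposed here.

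The cost is mainly a narrower claim: these are wording changes, and the month-2 evaluations are already scheduled in both arms. One consequence should be stated openly. N = 31 was not derived for a between-arm comparison, so the precision of that comparison should be reported as it is.

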***End-point evaluation***

**Neurocognitive evaluation**

The neurocognitive evaluation will be done at baseline and after 2 months for all patients. In the cross group a 3^rd^ evaluation will be performed after 4 month- after crossing and completing 2 months of HBOT treatment. Cognitive function will be assessed using the one-hour Mindstreams Computerized Cognitive Test Battery (Mindstreams; NeuroTrax Corp., NY). Detailed description of the tests can be found on Neurotrax website ([www.neurotrax.com](http://www.neurotrax.com)).

To minimize differences in age and education, each outcome parameter will be normalized and fit to an IQ-like scale (mean=100, S.D=15) according to patient's age and education. Normalized subsets of outcome parameters will be aggregated to produce four index scores relevant to mild TBI: **Memory, Attention, Executive function,** and **Information Processing Speed**.

Three different test versions exist in the Mindstreams testing battery to allow repeated administrations, test-retest reliability for those versions were evaluated and found high, with no significant learning effect [[23](#_ENREF_23),[24](#_ENREF_24)].

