**Sample Size Considerations**

Presentation of sample size is based on achieving 80% power overall to demonstrate that improvement rate in *mindstreams score* is at least 12%. An improvement rate of at least 10% in the neurocognitive score in treatment group (compared to baseline, prior to HBOT treatment) would be an appropriate clinical target for HBOT treatment success and of sufficient interest to encourage further investigation of HBOT treatment for post TBI patients suffering chronic neurocognitive deficiencies.

Sample size is based on the assumption that exposure to the *mindstreams* tests at baseline without any additional training might induce 2% score improvement in the second test, following treatment, (test-retest effect). Assuming a true success rate of 12% a sample of N = 31 will provide 80% power to show that HBOT treatment induces at least 10% improvement on *neurocognitive test score*. This is based on a power analysis using the normal approximation for the binomial, with one-sided Alpha=0.05.

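### The one-way cross gives no controlled within-group efficacy evaluation and does not address the missing placebo, although the Randomization section credits it with both

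*Protocol*

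**What the plan says.** The Randomization section explains why there is no placebo and then turns to the cross: "In order to somewhat compensate for this limitation, the control will be a cross group". It closes the argument with "The cross for treatment enables intra-group efficacy evaluation in both treatment and control group". The same section acknowledges that patients know their arm and that the quality-of-life evaluations are therefore not blinded.

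The Study protocol section sets the visits. For one arm: "The patients in the treated group will be evaluated twice – at baseline and after 2 months of HBOT treatment". The cross group is evaluated three times: "at baseline, after a 2 month control period of no treatment and after a consequent 2 month period of HBOT treatment". The crossover character is stressed: "We emphasize that the study will be a cross-over trial and patients in the cross group will receive HBOT treatment after their second evaluation". The Neurocognitive evaluation section places the third test at month 4, in the cross group only, "after crossing and completing 2 months of HBOT treatment".

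Two statements bear on retest effects. Sample Size Considerations assumes that baseline exposure "might induce 2% score improvement in the second test, following treatment, (test-retest effect". The Neurocognitive evaluation section says that the alternate test versions showed no significant learning effect. Neither gives a figure for a third test, and neither deals with expectation.

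**The concern.** A crossover earns its within-patient comparison by having sequences in both directions, so that treatment and period can be separated. Here there is one crossing sequence, no treatment then HBOT, and the treated group is not seen after month 2. The within-group evaluation claimed for both groups is therefore uncontrolled in each: in the treated group there is no control interval, and in the cross group nobody is untreated at month 4. Nor does the cross act on the missing placebo, because patients know when HBOT starts just as they know when they are not receiving it.

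This reaches beyond terminology. The Primary Efficacy Analysis Set requires a valid score following 2 months of HBOT, which for a cross patient is the month-4 score. The Primary Efficacy Analysis refers to a relevant cohort without defining it. Post-cross scores could thus enter an efficacy statement, and the Randomization section would be the justification for it.

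**Working it through.** The protocol states no figure for the post-cross evaluation, so there is none to reproduce. The check has two parts.

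**1. What each comparison estimates**

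Let m be the baseline mean, v2 and v4 the visit effects at months 2 and 4 (retest, time), and h the effect of open HBOT, including any expectation that comes with knowing one is treated.

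| Group | Month 0 | Month 2 | Month 4 |
|---|---|---|---|
| Treated | m | m + v2 + h | not measured |
| Cross | m | m + v2 | m + v4 + h |

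- Treated, before and after: v2 + h.
- Cross, month 2 to month 4: (v4 − v2) + h.
- Randomised contrast of changes to month 2: (v2 + h) − v2 = h.

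The parameter v4 appears in one cell only and always together with h. With v4 unrestricted, that cell fits itself and carries no information on h. In the cross group alone, the design matrix for intercept, two visit terms and HBOT has four columns and rank 3, so h is not estimable there.

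The standard error shows the same thing. Assumptions: SD 15 (the normative scale in the Neurocognitive evaluation section), equal correlation ρ between visits, a common baseline mean, and N = 31 split 16/15. With visit terms,

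SE(h) = 15 × √[(1 − ρ²)(1/16 + 1/15)],

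which is 4.67, 3.85, 3.23 and 2.35 points at ρ = 0.5, 0.7, 0.8 and 0.9. Generalised least squares gives the same values with the month-4 data included and with them left out. With 31 per arm, unit SD and separate group means, the equality also holds (0.254, 0.197 and 0.114 SD at ρ = 0.5, 0.7 and 0.9).

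**2. False-positive rate of a within-group test when h = 0**

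One-sided 5% paired t-test, SD of change = 15√[2(1 − ρ)], non-centrality = gain × √n / SD of change, rate read from the non-central t with n − 1 degrees of freedom. Example: ρ = 0.7 gives an SD of change of 11.62. For n = 16 and a 2-point gain, the non-centrality is 2 × 4 / 11.62 = 0.69 and the rate is 16%.

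| ρ | Treated, n = 16, 2 points | Cross months 2–4, n = 15, 0 points | 1 point | 2 points |
|---|---|---|---|---|
| 0.5 | 13% | 5% | 8% | 12% |
| 0.7 | 16% | 5% | 9% | 16% |
| 0.8 | 20% | 5% | 10% | 19% |
| 0.9 | 31% | 5% | 14% | 29% |

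The treated column uses the protocol's own 2% second-test gain, taken as 2 points on a scale with mean 100. The cross columns are a range, because no third-test gain is stated. Any expectation effect would add to every column. The protocol does not say whether 31 is the total or the number per arm. With 31 in the group the same formula gives 18% to 49% for a 2-point gain.

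**The case against.** Much can be said on the other side.

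- The protocol claims only partial compensation for the missing placebo and is open about the lack of blinding. That is fair, but the sentence on intra-group efficacy evaluation carries no such qualifier.
- The aliasing depends on leaving visit effects free. If they are absent or linear, HBOT is estimable from the cross group, and the statement on learning effects could be offered in support. That stands as a condition. Against it, the sample size section assumes a 2% retest gain, and neither statement covers expectation. Even a linear trend gains little: with 31 per arm and ρ = 0.7, the SE falls from 0.197 to 0.191 SD, about 3%.
- The cross group has its own control period. Its treated-period change minus its control-period change equals h + v4 − 2·v2. If practice is linear (v4 = 2·v2), this is h, and the one-sided 5% test keeps its level. If a 2-point gain stops after the second test, the bias is −2 points and the false-positive rate is 2.7% to 1.1% over ρ = 0.5 to 0.9 (n = 15, SD of the difference 15√[6(1 − ρ)]). So constant or diminishing practice does not inflate that comparison. This stands, and the fix uses it. Expectation remains in it, as it does in the randomised contrast.

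A reader might infer that the trial cannot identify an HBOT effect at all, or that the cross-group test is always inflated. Neither follows. The month-2 contrast identifies the effect of HBOT against open no treatment, and with no third-test gain or expectation the cross-group rate is the nominal 5%. A reader might also suppose that the protocol plans a pooled model without visit terms, or a formal test of the month-2 to month-4 change. It specifies neither. The crossover label alone is a matter of preference, since the visit schedule is set out clearly.

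**Conclusion.** The point holds in limited form. The Randomization section credits the cross with a property that the schedule lacks in both groups, and the cross does not address the missing placebo. With unrestricted visit effects, the month-4 data contribute nothing on HBOT; that result needs no assumption about the size of any visit effect. The false-positive figures do rest on assumptions: SD 15, ρ from 0.5 to 0.9, 2% read as 2 points and a 16/15 split. On these, the treated-group before-and-after test errs 13% to 31% of the time. The cross-group test errs between 5% and 29%, depending on a third-test gain that the protocol does not state. The change is worth making because it settles which comparison may support an efficacy conclusion, at a time when the definition of the efficacy set lets month-4 scores in.

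**What to change.** In the Randomization section, replace the two claims with a statement that efficacy conclusions rest on the randomised comparison of treated and cross groups from baseline to month 2. State there that within-group changes (treated before and after, cross month 2 to month 4) are supportive and descriptive and do not confirm efficacy.

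Add two conditions:
- If month-4 data enter any efficacy model, the model includes a categorical visit effect.
- If a comparison within the cross group is reported, it sets the treated-period change against the same patients' control-period change and states what it assumes about visit effects.

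Describing the design as delayed-treatment instead of crossover is optional.

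The cost is wording only: no added patients, visits or procedures. The downside is that the post-cross gain can no longer be cited as independent evidence of efficacy.

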**Brain functional Imaging - SPECT imaging and Analysis**

Single photon emission computed tomography (SPECT) will be conducted before and after HBOT. Subjects will lay supine in a quiet dimly lit room for 20 min prior to injection of the radiopharmaceutical. Apart from administration of the injection by a physician, they will remain alone in the room during this period. Subjects will be asked to remain at rest for 10 min after the injection of the radiopharmaceutical to allow uptake of the radiopharmaceutical in the brain.

An injection of 925-1110 MBq (25-30 mCi) of technetium-99m ethyl cysteinate dimmer (Tc-99m-ECD) will be given into an arm vein through a previously placed intravenous cannula. SPECT imaging of the brain will be performed, at 40-60 min post injection, with the subject’s head supported by a headrest, using a dual detector gamma camera (ECAM or Symbia T, Siemens Medical Systems) equipped with high resolution collimators. Data will be acquired in the step-and-shoot mode, using a 360 degree circular orbit, with the detectors of the gamma camera as close as possible to the subject’s head. The camera used for imaging will be noted for each subject and the same camera will be used for the follow-up study. Data will be acquired using a 128׳128 image matrix in 3 degree steps of 20 seconds per step. Data will be reconstructed by iterative reconstruction with no filtering. The Chang method (*μ*=0.12/ cm) will be used for attenuation correction.

Intra subject visual analysis will be conducted using a process in which pre and post treatment studies are fused and normalized to pre-treatment whole brain activity.

Visual analysis will be carried out by two nuclear medicine physicians who compared the scans independently and grad them as either: 1=no change, 2=mild change and 3=significant change. Where, no change is assign when no visual difference is noted in the number or size of perfusion deficits, mild change is given when a reduced number of perfusion defects are noted or the size of the perfusion defects is reduced. Significant change should be attributed when a global perfusion increment is observed in addition to diminution of defect numbers or size. Differences in evaluation will be resolve after reviewing the images together. Scan visual interpretation will be carried out while blinded to any laboratory or clinical data.

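### Complete blindness is overstated for both primary endpoints: Mindstreams is performed by patients who know their arm, and masking of SPECT readers to arm and scan order is not specified

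*Protocol*

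**What the plan says.** The protocol's Randomization section states that "There will be no placebo in the cross group during the control period" and explains at length why a sham was not used. It then says of the patients that "they will not be blinded with regard to the treatment arm", and draws one consequence: "Accordingly, the quality of life evaluations will not be blinded". The next sentence claims that "the complete blindness evaluation can be assured in both of the primary end points of this study", and names the Mindstreams computerized evaluation and the SPECT reading.

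On the first endpoint, the Neurocognitive evaluation section says: "Cognitive function will be assessed using the one-hour Mindstreams Computerized Cognitive Test Battery". The index scores cover memory, attention, executive function and processing speed.

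On the second, the SPECT section says that "pre and post treatment studies are fused and normalized to pre-treatment whole brain activity". Two nuclear medicine physicians grade each comparison independently and settle differences together. On masking it says: "Scan visual interpretation will be carried out while blinded to any laboratory or clinical data". There are three grades: no change, mild change and significant change. On the middle one it says that "mild change is given when a reduced number of perfusion defects are noted or the size of the perfusion defects is reduced". The top grade adds a global rise in perfusion. There is no grade for worsening.

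**The concern.** The paragraph accepts that patients are unblinded but applies this only to quality of life. A performance test taken by the same patient is exposed to the same knowledge. Someone who has attended 40 sessions and expects to be better may try harder or approach the test differently. Someone who knows that they are waiting for treatment may do the reverse.

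This matters most for Mindstreams. It is the only primary endpoint for which the protocol states a hypothesis, a sample size and a success rule. The blindness sentence is also the only assurance given against expectation bias. If it stands, a report could describe both primary endpoints as blinded and read a Mindstreams gain as the effect of oxygen, although the design cannot separate oxygen from expectation and attendance.

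For SPECT the stake is smaller but real. A reader who knows which scan is the later one, and who has no grade for deterioration, can only record stability or benefit.

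**Working it through.** No figure in the protocol supports the blindness claim, so there is none to reproduce. The check sets the sections side by side.

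**Mindstreams**

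1. Who knows the arm? The patient does, in both groups and in both periods (Randomization).
2. Who produces the score? The patient does, by performing the battery (Neurocognitive evaluation).
3. What does computer testing protect? It protects administration and scoring, because no rater's judgement enters. It does not act on the performance itself.
4. From 1 to 3, blinding is at most on the assessor's side, and the word complete does not hold.
5. Does the analysis allow for the gap? The Primary Efficacy Analysis names two sources of improvement: HBOT (p1, assumed 0.12) and test-retest (p2, assumed 0.02). Expectation and attendance have no term, so any gain from them would be counted within p1.
6. Does the comparison remove it? Success is declared when the lower confidence limit for HBOT success in the relevant cohort is at or above 0.12, and the Randomization section also relies on within-group evaluation. Both rest on before/after change in patients who know that they were treated. A contrast with the untreated control period would not remove the effect either, because those patients know that they are untreated.

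**SPECT**

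1. What is masked? Laboratory and clinical data. Arm and scan order are not named. Arm may be meant to fall under clinical data, but the text does not say so.
2. Does the scale need scan order? Yes. A reader cannot call defects reduced, or perfusion increased, without knowing which scan is the reference. This is stronger evidence than the normalization step, which describes how the images are processed and not what the reader sees.
3. Is order the same as arm? Not in general. The Study protocol section gives the cross group imaging at baseline, after the control period and after HBOT, so control-period pairs exist. If they are read alongside HBOT pairs, knowing the order does not reveal the arm. The SPECT section, however, describes scans only before and after HBOT. Within such a pair, later means treated.
4. From 1 to 3, masking is present in part and is incompletely specified.

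**Size**

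The documents give no expectation effect for Mindstreams. The success rule concerns a proportion, whereas the battery is scaled to mean 100 and SD 15. An assumed shift in points therefore does not translate into a change in the success proportion without further assumptions that this document does not support. No number is attached here.

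**The case against.** The best defence is that the sentence speaks of blind evaluation and names the computerized test and the image reading. It can be read as a claim about assessors only, made straight after the lack of patient blinding is admitted. The protocol also treats the missing placebo openly, as a limitation. Part of this stands: assessor-side protection exists for both endpoints, and the decision not to use a sham is argued and is not the fault here. What does not stand is the word complete, or the step that confines the consequence of unblinded patients to quality of life.

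Four stronger readings are tempting, and the protocol does not support them:

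- A reader might infer that there is no protection at all. Computer scoring, and independent dual reading masked to laboratory and clinical data, are real safeguards.
- A reader might infer from the normalization step that scan order is shown to the SPECT readers. The protocol does not say what labels or order they see. That they must know it is an inference, and it rests better on the grading scale.
- A reader might treat known order as known arm. Control-period pairs break that link if they are read together with the others.
- A reader might say that the protocol attributes the effect to oxygen alone. It does not. The concern is that the blindness sentence would lend support to such a conclusion.

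**Conclusion.** The point holds in a limited form. The claim of complete blindness is wrong for Mindstreams on the protocol's own facts, and confidence in that part is high. For SPECT the masking is incomplete as specified: arm and order are not named, and the scale presupposes order. Confidence is lower there, because the actual reading conditions are not described and arm may have been meant under clinical data.

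The direction of concern is towards overstating benefit. This assumes that patients who know they are treated expect to improve, and that effort or expectation can move a cognitive test score. The size cannot be derived from the documents. Nothing here shows that a result would be false. It limits what a positive result may be said to mean. The correction should be made, and it does not require a change to treatment or the addition of a sham.

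**What to change.** 1. Replace the blindness sentence with: *Mindstreams is scored automatically but performed by unblinded patients; SPECT is read by assessors masked to arm and scan order.* The SPECT half becomes true only once step 3 is adopted.
2. State that a Mindstreams improvement, including one that meets the success rule, reflects the HBOT programme with expectation and attendance effects included, not oxygen alone.
3. For SPECT:
   - Code the pairs, mix control-period pairs with HBOT pairs, and randomise scan order within each pair.
   - Use a normalization that does not reveal order, for instance to whichever scan is labelled A. It must still show a global perfusion difference, because the top grade depends on one.
   - Grade A against B on a two-directional scale (better, same, worse) and decode after reading. The scale has to change together with the order masking, since the present grades cannot be applied without knowing the order.

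The cost is a more modest claim, plus a small amount of work to code the scans and revise the grading scale.
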